**Fig. 1 Fig1:**
[figure not shown]
Study flowchart. TFI, Tinnitus Functional Index; ST, somatic tinnitus; FUV, follow-up visit; uMARS, user version of Mobile Application Rating Scale

### Outcome measures

The following outcome measures will be collected at baseline and during the two follow-up visits. The first follow-up visit is planned 1 month (range: 4 to 7 weeks) after the last treatment session. The second follow-up visit will take place 3 months (range: 8 to 13 weeks) after the last treatment session. In between the first and second follow-up moment should be a minimum period of 4 weeks. For certain outcome measures additional measuring moments are planned, these are specified individually below. See Fig. 2 for an in-detail schedule of enrolment, interventions and assessments in accordance with the SPIRIT 2013 guidelines [30].

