##### Questionnaires related to the cost-effectiveness analysis

EuroQoL (EQ)-5D [58]

The EuroQoL EQ-5D questionnaire is the most commonly used method to collect health-related Quality of Life (HRQOL) data and is recommended by worldwide economic evaluation guidelines such as the NICE recommendations [59, 60]. This questionnaire measures HRQOL using 5 dimensions: mobility, self-care, usual activities, pain/discomfort and anxiety/depression [58]. The response pattern produces a code which represents a health state of the participant. Each health state is associated with a health utility value between 0 and 1 in which 0 represents death and 1 corresponds to perfect health [60]. To calculate utility values, the recently published utility value sets for Belgium will be used [61]. HRQOL is necessary to calculate quality-adjusted life years (QALYs), the most important outcome from the health economics point of view [60]. The five level (5 L)-version is preferred over the three level (3 L)-version as it is more nuanced and thus more sensitive to gains (or losses) in general health [62]. The EQ-5D-5L will be assessed at baseline and both follow-up moments and will additionally be collected after the final treatment session.Productivity Cost Questionnaire (*i*PCQ) [63]

The iMTA Productivity Cost Questionnaire (*i*PCQ) includes three modules measuring productivity losses of paid work due to (1) absenteeism and (2) presenteeism (productivity loss due to paid work) and productivity losses related to (3) unpaid work. The *i*PCQ delivers the necessary input to calculate productivity loss. *i*PCQ will be collected monthly, meaning every 3 to 5 weeks. To organise this systematically, patients of the intervention group will be asked to complete this questionnaire at treatment session two, four and six and patients of the control group at treatment session four, eight and twelve. Both groups will additionally receive the *i*PCQ at 1 month follow-up and 3 months follow-up, as defined above. An additional two-month follow-up moment is planned for the *i*PCQ (range: 3 to 5 weeks after 1 month follow-up assessment).

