##### Costs

In accordance with the European Network for Health Technology Assessment (EUnetHTA) guidelines, the CEA will comprise two parts: a base case analysis, which only takes into account direct medical costs, and an extended analysis, which additionally considers relevant indirect costs such as work absenteeism and productivity loss [68]. As all relevant direct medical costs (i.e. consultation fees, scans, medication, etc.) stem from inpatient care provision, the costs for the base case analysis will be collected using the financial records of the Antwerp University Hospital. Relevant medication use is registered as a standard practice in the RCT described above. To assign costs to medication use, we will use the official unit prices of the Rijksinstituut voor Ziekte- en Invaliditeitsverzekering (RIZIV)/ l’Assurance soins de santé et indemnités (INAMI). As discussed above, patients are allowed to seek medical help outside the hospital between the two follow-up moments. As a consequence, healthcare and medication use cannot be monitored using hospital’s financial records in this period of time. Therefore, patients will keep a diary specifically designed for this study in which they should report all information regarding tinnitus related medical help and medication use. The content of this diary is discussed elaborately above.

Apart from the direct medical costs, the CEA will also incorporate relevant indirect costs in a separate, extended analysis. The abovementioned *i*PCQ will be used to collect the necessary input to calculate the costs associated to absenteeism and productivity loss due to tinnitus complaints following the Human Capital Approach (HCA) [68]. The HCA values the time during the whole period of work inability due to sick leave by multiplying the total number of days of work absenteeism by the national average labour cost per day. To calculate the productivity loss at work, the number of days with productivity loss will be multiplied by efficiency loss and the daily average of hours worked. Next, to value the productivity loss, this result will be multiplied by the national average labour cost per hour. All cost data will be collected over the entire study period starting at baseline.

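### The follow-up windows permit schedules that break the iPCQ's own spacing and order, and leave the cost and QALY horizon varying by five weeks between patients

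*Protocol article*

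**What the plan says.** Under Outcome measures, both visits are counted from the end of treatment: "The first follow-up visit is planned 1 month (range: 4 to 7 weeks) after the last treatment session" and "The second follow-up visit will take place 3 months (range: 8 to 13 weeks) after the last treatment session". A spacing rule follows: "In between the first and second follow-up moment should be a minimum period of 4 weeks".

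Under Questionnaires related to the cost-effectiveness analysis, the iPCQ "will be collected monthly, meaning every 3 to 5 weeks". During treatment it is tied to session numbers. For the experimental arm the text reads: "patients of the intervention group will be asked to complete this questionnaire at treatment session two, four and six". The control arm has its forms at sessions 4, 8 and 12. The third form in each arm therefore coincides with the final session. After treatment it is given at both follow-up visits and at a two-month point ("range: 3 to 5 weeks after 1 month follow-up assessment").

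Under Costs, the accrual period is described only in words: "All cost data will be collected over the entire study period starting at baseline". The diary of outside care covers the time between the two follow-up visits (Diary of medical costs). The EQ-5D-5L is taken at baseline, after the final session and at both follow-ups.

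**The concern.** The iPCQ has a fixed spacing rule, but it is attached to visits whose windows were set separately and are wider. Three intervals after treatment should each be 3 to 5 weeks: final session to first follow-up, first follow-up to the two-month form, and the two-month form to second follow-up. If the visit windows do not allow this, some patients will have long uncovered stretches. Others will have forms that fall close together or out of order. The article does not state the iPCQ look-back period. Under any fixed look-back, gaps lose productivity loss and overlaps count it twice.

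The horizon is a second matter. Costs and QALYs both grow with time observed. If the end of observation moves with the date of the second visit, patients are summed over different lengths of time, and any difference between arms in that length enters both parts of the ICER.

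**Working it through.** **Inputs** (weeks after the last session, from the sections cited above). First follow-up F1 = 4 to 7. Second follow-up F2 = 8 to 13, with F2 − F1 ≥ 4. Two-month iPCQ M = F1 + 3 to F1 + 5. Required iPCQ spacing 3 to 5.

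**Visit windows alone.** The earliest F2 is 4 + 4 = 8, as stated. The latest F1 gives 7 + 4 = 11, which lies within 13. The two visit windows are consistent with each other.

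**Final session to first follow-up.** The permitted interval is 4 to 7 weeks and the rule is 3 to 5. Any first follow-up later than week 5 breaks the rule.

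**Order of the two-month form and the second visit.** M can be as late as F1 + 5 and F2 as early as F1 + 4, so M can follow F2 by at most 1 week. Example: F1 = 4, F2 = 8, M = 9. In whole weeks:

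- F1/F2 pairs: 6 + 5 + 4 + 3 = 18 for F1 = 4, 5, 6, 7. With three choices of M, 18 × 3 = 54 combinations.
- M after F2 (M = F1 + 5, F2 = F1 + 4): one per F1, so 4 of 54 (7%).
- M in the same week as F2 (M − F1 and F2 − F1 both 4, or both 5): two per F1, so 8 of 54.

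Counting calendar days gives the same picture. Reversal is possible for 154 of 561 permitted visit pairs (27%). Of 8,415 permitted day triples, 616 (7%) are reversed and a further 2% fall on the same day.

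**All three intervals together.** Two gaps of at least 3 weeks after F1 need F2 − F1 ≥ 6, but the plan requires only 4. In whole weeks, 4 + 3 + 2 + 1 = 10 of 18 visit pairs meet this (by day, 45%). Adding F1 ≤ 5 leaves 4 + 3 = 7 of 18. For the other 11 pairs no two-month date satisfies every iPCQ interval.

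**Horizon and diary period.** The end of observation varies by 13 − 8 = 5 weeks between patients. The diary period runs from 4 weeks to 13 − 4 = 9 weeks. At an assumed utility of 0.6 to 0.9, five weeks are 5/52 × 0.6 to 5/52 × 0.9 = 0.058 to 0.087 QALY.

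**Between arms, conditional.** First to last session is (6 − 1) × 2 = 10 weeks in the experimental arm and (12 − 1) × 1 = 11 weeks in the control arm. If session 1 comes equally soon after baseline in both, observation ends 18 to 23 against 19 to 24 weeks after session 1, and the treatment-period iPCQ falls at weeks 2, 6, 10 against 3, 7, 11. One week is 0.012 to 0.017 QALY at the same utilities. The annual costs quoted in Background give 1544/52 to 3429/52 = 30 to 66 euro per week for healthcare. With indirect costs added, (1544 + 2565)/52 to (3429 + 3702)/52 = 79 to 137 euro. Those costs describe tinnitus patients in general, so they show scale only.

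**The case against.** Much can be said for the plan. Staff are unlikely to send a two-month form after a three-month visit, and the article refers to a detailed schedule in Fig. 2, which is not available here. A horizon calculation is often left to a health-economic plan. Counting from the last session is deliberate: Primary outcome measure justifies it by the largest effect being expected one month after treatment. These points stand, and they are reasons not to move the primary visit. They do not reconcile the ranges printed in the text.

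A reader might go further in four ways that the documents do not support.

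- **The two visit windows contradict each other.** They do not; the conflict is between the iPCQ rules and those windows.
- **12 of 54 combinations (22%) is how often the order reverses.** Eight of the 12 are ties, and none of these counts is a forecast.
- **The experimental arm is necessarily observed for one week less.** Both arms are described as 12-week programmes. If experimental session k falls at week 2k and control session k at week k, the iPCQ sessions align at weeks 4, 8 and 12 and the difference is zero. Even if it exists, it lowers both costs and QALYs in that arm, and no net bias in the ICER is shown. With no QALY standard deviation in the article, its size relative to sampling error cannot be stated.
- **Adherence drives the timing of the primary outcome.** Secondary analysis puts the per-protocol population first, which largely removes early stoppers. The article does not say when they are assessed, so any effect on the intention-to-treat sensitivity analysis is inference.

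**Conclusion.** The point holds as an inconsistency between the iPCQ rules and the visit windows, and it follows from the printed ranges without outside assumptions. The final-session to first-follow-up interval can be up to 2 weeks too long. The two-month form can fall on the second visit or up to one week after it. In 11 of 18 whole-week visit pairs the iPCQ spacing cannot be met throughout. Compliant schedules do exist, for example weeks 4, 8 and 12, so the fault lies in what the windows permit.

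The 5-week variation in horizon and the 4-to-9-week diary period also follow from the text. The one-week difference between arms rests on an equal delay to session 1 and should be treated as a possibility to close off. The iPCQ part affects the extended cost-effectiveness analysis. The horizon affects the base case and the QALYs as well. The sample size is unaffected, and the non-inferiority comparison is not shown to be.

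**What to change.** Keep the primary TFI visit one month after treatment, and change the following.

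1. Require the second follow-up at least 6 weeks after the first, and the two-month iPCQ at least 3 weeks before it (and at most 5, to keep the monthly rule).
2. Narrow the first follow-up to weeks 4 to 5, or add an iPCQ when it falls later. Narrowing is cleaner: two intervals of at least 3 weeks fit only from week 6, and a first follow-up at week 7 would leave only week 13 for the second.
3. Schedule the treatment-period iPCQ by study week, the same weeks in both arms, instead of by session number.
4. Compute costs and QALYs over one fixed horizon from baseline, common to both arms, using actual dates: area under the utility curve and costs per day. State in advance how a patient whose last visit falls before that horizon is handled.

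Items 1 to 3 are a small amendment, and the price is slightly tighter visit scheduling. Item 4 is analysis only and also removes any one-week difference between arms from the comparison.

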**Fig. 2 Fig2:**
[figure not shown]
Schedule of enrolment, interventions and assessments in accordance with the SPIRIT 2013 guidelines

#### Primary outcome measure

The primary outcome is the change in Tinnitus Functional Index (TFI) score from baseline to 1 month after the treatment. This time point was chosen since previous research indicated that the largest treatment effect on TFI is to be expected 1 month after the last treatment session [37–40]. For the cost-effectiveness analysis, an additional time point, immediately after the last treatment session, is added to be able to link the amount of decrease on TFI to the EuroQoL (EQ)-5D-5L that assesses HRQOL. The TFI is a self-report questionnaire comprising 25 questions, each scored on an eleven-point Likert scale, objectifying the impact and severity of tinnitus. Eight subscores are differentiated, namely intrusiveness, sense of control, cognitive complaints, sleep disturbance, auditory difficulties, relaxation, quality of life (QOL) and emotional distress. The total score and subscores will be noted on a scale of 0 to 100 with higher scores indicating higher levels of tinnitus-related distress [33, 34]. A change of 13 points out of 100 is considered a clinically relevant change [33]. TFI has a high sensitivity to change, a good test-retest reliability (*r*: 0.78), discriminant validity with the Beck Depression Inventory-Primary Care (*r*: 0.56) and convergent validity with both the Tinnitus Handicap Inventory (THI) (*r*: 0.86) and the visual analogue scale (VAS) for tinnitus loudness (*r*: 0.75) [33, 41, 42].

#### Secondary outcome measures

##### Clinical cervical and temporomandibular outcome measures

The following tests will be used to assess the dysfunction of the cervical spine and temporomandibular area. Firstly, cervical spine mobility and joint repositioning accuracy (JRA) will be measured using the NeckCare Unit (https://www.neckcare.com/). This device, using accelerometer and gyroscope data, is specifically designed for investigating the cervical range of motion and JRA. Additionally, the strength and coordination of the deep neck flexor and extensor muscles and the shoulder stabilising muscles will be assessed according to the standardised protocol proposed by Segarra et al. [43].

The mobility of the temporomandibular joint will be measured using a ruler. Mouth opening, protrusion and laterotrusion will be objectified in this manner. Finally, active myofascial trigger points will be looked for in the masseter and temporalis muscle and in the sternocleidomastoid, splenius capitis, upper trapezius and levator scapulae muscles [44, 45].

##### Audiological outcome measures

Pure tone hearing thresholds

Pure tone audiometry, to objectify the presence of hearing loss, will be performed according to current clinical standards (ISO 8253-1, 1989) using a two-channel Interacoustics AC-40 audiometer in a silent room. Air conduction thresholds are measured by the use of headphones at 125 Hz, 250 Hz, 500 Hz, 1 kHz, 2 kHz, 3 kHz, 4 kHz, 6 kHz and 8 kHz. In cases where air conduction thresholds exceed the normality level of 20 dB HL at one or more frequencies between 250 Hz and 4 kHz, bone conduction thresholds will be measured at 250 Hz, 500 Hz, 1 kHz, 2 kHz, 3 kHz and 4 kHz.Speech-in-quiet (SPIQ) and speech-in-noise (SPIN) understanding

Speech reception in quiet (SPIQ) will be measured using the Dutch open-set NVA lists developed by the Nederlandse Vereniging voor Audiologie (NVA) (Dutch Society for Audiology) [46]. Each list consists of twelve monosyllabic words (consonant-vowel-consonant), of which one is a training item. The speech recognition score is the percentage of correctly identified phonemes. The lists will be presented through headphones. The speech reception in noise (SPIN) will be assessed by means of the Leuven Intelligibility Sentences Test (LIST) using an adaptive procedure [47]. The frequency spectrum of the noise signal is equal to the long-term average speech spectrum of the sentences. The level of the noise is fixed at 65 dB SPL, while the level of the speech signal is altered depending on the response of the patient. If the participant repeats the keywords of the sentence correctly, the level of the next sentence is decreased by 2 dB SPL. If the participant fails to repeat the keywords correctly, the level is increased by 2 dB SPL. Each list consists of ten sentences, and the speech reception threshold (SRT) is calculated as the mean level of the last five sentences together with the level of the imaginary 11th sentence of the list. This speech in noise test is performed using headphones.Psychoacoustic tinnitus measures

**Tinnitus pitch matching**

The pitch is the psychoacoustic equivalent of the physical parameter frequency. The tinnitus pitch is obtained by use of a pitch matching technique which is the quantitative and qualitative description of the spectral characteristics of the tinnitus. For this technique, a two-alternative forced-choice procedure will be used using the contralateral ear as the reference ear. In cases where tinnitus is perceived bilaterally, the choice of the ear is the side where the tinnitus is perceived the loudest. By this technique, an attempt is made to identify the centre pitch of the tinnitus. When multiple tinnitus sounds are perceived, it is suggested to concentrate on the most troublesome tinnitus sound. Each time, a pair of pure tones (or noises in case of noise-like tinnitus), differing by one or more octaves, are presented to the subject, who has to indicate which of the tones resembles the tinnitus the most. This procedure is repeated, and finer adjustments are made to obtain a match of tinnitus pitch as exact as possible.

**Tinnitus loudness matching**

Loudness is the perceptual correlate of the sound intensity. The tone (or noise) defined as the pitch math is presented to the ipsilateral ear (when appropriate), and a loudness match is made by the use of an alternating forced-choice procedure with an accuracy of 1 dB.

##### Questionnaires related to the effectiveness analysis

VAS for tinnitus loudness

Patients are asked to score the mean and maximum loudness of their tinnitus in the previous week on a 100-mm horizontal line ranging from left: 0 (absence of tinnitus) to right: 100 (as loud as possible, cannot be any louder) [48].Neck Bournemouth Questionnaire (NBQ) score

The presence and severity of neck complaints will be evaluated using the NBQ. The NBQ [49] consists of seven questions on the severity of the neck complaints and its interference with the patient’s wellbeing and professional and daily activities. Each item is scored on an eleven-point Likert scale. A higher score out of the maximum of 70 represents higher levels of neck pain and disability [49]. Scores from 13 points upwards are considered to represent a clinically important neck dysfunction [49]. The test-retest reliability of the NBQ is moderate (ICC: 0.65). The construct validity is acceptable with both the Neck Disability Index (*r*: 0.50) and the Copenhagen Neck Functional Index (*r*: 0.44). The effect size was high (Cohen’s *d*: 1.67), which indicates that the NBQ is highly responsive to changes in cervical spine complaints [49–51]. The clinically relevant change of the NBQ is a 12 points decrease [49, 50].Temporomandibular disorder (TMD) pain screener score

The presence and severity of temporomandibular disorders (TMD) will be evaluated using the TMD pain screener. The TMD pain screener is a 6-item questionnaire regarding pain complaints from the orofacial region and their dependency on functions, like opening wide or chewing. One item has three answer options, scored zero, one or two. The five remaining items are answered dichotomously with yes or no, respectively scored as one or zero. The minimal score is zero and the maximal score is seven. In case a patient scores at least a three out of seven on the TMD pain screener, the patient is suspected to suffer from a painful TMD (sensitivity 0.99 and specificity 0.95–0.98, respectively) [52]. Internal consistency of the questionnaire is excellent, with a coefficient *α* value of 0.93, reliability is good (ICC: 0.79), and excellent sensitivity and specificity for diagnosing TMD (0.99 and 0.95-0.98, respectively) [51, 53].Hospital Anxiety and Depression Scale (HADS)

The Hospital Anxiety and Depression Scale (HADS) is used to detect signs of depression and anxiety symptoms [54]. It is a self-assessment scale and was developed to identify the possibility and probability of the presence of anxiety and depression among patients in non-psychiatric clinics [54]. It exists of two subscales, an anxiety subscale (HADS-A) and a depression subscale (HADS-D), both containing seven intermingled items. Each subscale is scored out of a total of 21; a score greater than eight indicates the presence of anxiety or depression symptoms, respectively [54]. A high internal consistency was stated for a both the depression and anxiety scale, with respectively a mean coefficient *α* value of 0.83 and 0.82 [55]. In addition, both scales also demonstrated a good sensitivity and specificity of approximately 0.80 [55]. The HADS is found to be an instrument of moderate reliability (ICC: 0.56) for screening states of depression and anxiety in the setting of a hospital medical outpatient clinic [51, 54, 55].Hyperacusis Questionnaire (HQ)

Hyperacusis, a symptom that often co-occurs with tinnitus, is quantified and characterised using the Dutch version of the Hyperacusis Questionnaire (HQ) [47, 56]. This questionnaire consists of 14 questions that are answered on a 4-point scale, ranging from ‘No’ (0 points), ‘Yes, a little’ (1 point), ‘Yes, quite a lot’ (2 points) to ‘Yes, a lot’ (3 points). Scores on the HQ consequently range from 0 to 42, and the traditional cut-off value for hyperacusis is 28 points [47]. Moderate correlations between the HQ, uncomfortable loudness levels and other health questionnaires and a high internal consistency of the HQ have been demonstrated [57].

##### Questionnaires related to the cost-effectiveness analysis

EuroQoL (EQ)-5D [58]

The EuroQoL EQ-5D questionnaire is the most commonly used method to collect health-related Quality of Life (HRQOL) data and is recommended by worldwide economic evaluation guidelines such as the NICE recommendations [59, 60]. This questionnaire measures HRQOL using 5 dimensions: mobility, self-care, usual activities, pain/discomfort and anxiety/depression [58]. The response pattern produces a code which represents a health state of the participant. Each health state is associated with a health utility value between 0 and 1 in which 0 represents death and 1 corresponds to perfect health [60]. To calculate utility values, the recently published utility value sets for Belgium will be used [61]. HRQOL is necessary to calculate quality-adjusted life years (QALYs), the most important outcome from the health economics point of view [60]. The five level (5 L)-version is preferred over the three level (3 L)-version as it is more nuanced and thus more sensitive to gains (or losses) in general health [62]. The EQ-5D-5L will be assessed at baseline and both follow-up moments and will additionally be collected after the final treatment session.Productivity Cost Questionnaire (*i*PCQ) [63]

The iMTA Productivity Cost Questionnaire (*i*PCQ) includes three modules measuring productivity losses of paid work due to (1) absenteeism and (2) presenteeism (productivity loss due to paid work) and productivity losses related to (3) unpaid work. The *i*PCQ delivers the necessary input to calculate productivity loss. *i*PCQ will be collected monthly, meaning every 3 to 5 weeks. To organise this systematically, patients of the intervention group will be asked to complete this questionnaire at treatment session two, four and six and patients of the control group at treatment session four, eight and twelve. Both groups will additionally receive the *i*PCQ at 1 month follow-up and 3 months follow-up, as defined above. An additional two-month follow-up moment is planned for the *i*PCQ (range: 3 to 5 weeks after 1 month follow-up assessment).

